#### Quality control of culture media

Sterile saline solution at 0.9% will be used to control the sterility of the culture medium and *Pseudomonas aeruginosa* ATCC 27853 and *Bacteroides fragilis* ATCC 25285 strains to evaluate the recovery capacity of facultative microorganisms and strict anaerobes. Each new batch of culture medium prepared will undergo this quality control.

### Phenotypic characterization

The phenotypic identification of the species will be carried out through mass spectrometry using MALDI-TOF MS equipment (Bruker Biotyper^®^, Germany*)*. The score used for reliable identification of pathogens will follow the manufacturer’s instructions.

### Genotypic characterization

The microorganisms isolated from cultures will be subjected to PCR analysis performed in two phases, as described by Barnard et al. [28]. The first to confirm the presence of bacteria (target and non-target) by using species-specific primers targeting the rRNA-16s and a second one, Multiplex-PCR, targeting the virulence and oxidative gens.

### Multiomic analyses

#### Whole genome sequencing

For the WGS, the DNA of the isolated *C*. *acnes* strains will be obtained with the Qiagen Blood & Tissue DNA extraction kit (Qiagen^®^, USA) and subsequent sample purification using RNase.

The extracted and purified DNA will be dosed, and adjusted to a concentration of 0.2 ng/μL. The ends of its two ribbons will be fragmented and tagged (forward and reverse 5’-3’). This will form fragments of different sizes. This data will be used to create a database on the Nextera Flex Kit platform (Ilumina^®^, USA). The samples will then be multiplexed into a cell stream and run on the NextSeq sequencer (Ilumina^®^, USA) using paired sequencing to generate files in fastq format files, which will then be filtered using the Trimmomatic tool version 0.36, as recommended by Bolger et al. [54]. This step will be critical for controlling the quality of the analysis because it reduces the possibility of errors during sequencing and allows the use of more reliable reading codes.

The obtained fragments will be sequenced, and their quality will be evaluated with the FastQC tool version 0.11.9. The RedDog software version 1.11 will be used to identify single nucleotide polymorphisms (SNPs) using the GCA_000008345.1 *C*. *acnes* reference strain deposited in the GenBank NCBI [https://www.ncbi.nlm.nih.gov/nuccore/] as a comparison. Finally, the PATRIC software version 3.5.21 will be used to create a complete genome phylogeny from the concatenation of SNPs.

#### Proteomics

In this study, proteomics approaches will apply gel-free and in-gel protein digestion by using sodium dodecyl sulfate polyacrylamide gel electrophoresis (SDS-PAGE) technique [2].

Thioglycolate culture mediums will be centrifuged, and the sediment obtained will be washed in phosphate buffer and centrifuged again. The sediment will be dissolved in a lysis solution containing 8 M urea, 2% 3-[(3-cholamidopropyl) dimethylammonio]-1-propanesulfonate, and 40 mM Tris (hydroxymethyl) aminomethane. This lysis will be complemented with the use of glass beads under a Bead Beater agitation (Biospec Product^®^, USA) (3 × 20 s with intervals of 20 s) followed by cooling for 5 min on an ice bath, as described by Shah et al. [55]. Protein concentration will be measured and 20 μg will be used for both the gel and solution techniques.

The SDS-PAGE -based technique will be used to evaluate the profile of the proteins present in the extract. Proteins will be removed from the gel with a sterile scalpel, eluted, and trypsinized (proteolic digestion) for further analysis through mass spectrometry. In the solution technique, the obtained extract will be trypsinized for further analysis through mass spectrometer. Regardless of the technique used, a nano-Liquid Chromatography coupled to a high-resolution mass spectrometer (nLC-HRMS) will be used.

After analysis by both techniques, the raw data (.*raw*) will be converted into a mascot general file (.*mgf*) using the Mascot Distiller software version 2.8.0, and proteins will be identified using protein banks referring to *C*. *acnes* and eukaryotes (humans), both created using the NCBI as a *fasta* extension. After this identification, the data will be validated using the Scaffold software version 5 for the same databases. Two biological replicas will be made for both the gel and solution technique. The Interactivenn.net [http://www.interactivenn.net/index.html] [56] and STRING version 11 software [57] will be used for comparative analysis and functional interaction of proteins, respectively.

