## Hypotheses and objectives

Our hypothesis is that LDD and LBP are related to LIVD colonization by *C*. *acnes*.

The primary goal of this study is to determine the incidence of LIVD colonization by low virulent pathogens using specific sampling and culture techniques, as well as phenotypic and genotypic techniques for microbiological characterization.

Other objectives of the study include: 1- assessing the possibility of clinical specimen contamination in positive cultures; 2- establishing a correlation between the presence of the pathogen and the clinical and radiological profile (Modic type 1 changes) of the study participants; 3- to outline a phylotypic profile of the most isolated *C*. *acnes* strains by bacterial WGS; and 4- identify a molecular profile for LDD and LBP in patients with positive cultures for *C*. *acnes* through proteomic and metabolomic techniques.

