**Fig 1 pone.0271773.g001:**
[figure not shown]
Flowchart showing all stages of the study.

The clinical specimens collected will be:

Peripheral blood. A 10 mL aliquot will be obtained 30 min after the infusion of surgical antibiotic prophylaxis through upper limb venoclysis. This sample will be placed in a tube containing clot activator for further separation of the serum, which, in turn, will be stored at −80°C for further analysis.Skin swab. After skin asepsis with 2% chlorhexidine gluconate degerming solution and 0.5% chlorhexidine gluconate alcoholic solution, a swab will be collected from the region where the surgical incision will be performed.Intervertebral disc. Five fragments will be collected at each level approached during surgery. A set of sterile surgical tweezers will be used exclusively for collection, one for each tissue fragment collected. The forceps with tissue fragment will be given to a member of the laboratory who will monitor the procedure inside the operating room immediately after collection. Each fragment will be placed in a vial containing thioglycolate broth (Merck^®^, Brazil) and 20 glass beads. The vials will be labeled with the initials of the study participants and the type of clinical specimen. After collection, the vials containing the clinical specimens will be kept at room temperature (18°C to 22°C) and transported in a specific case to the laboratory within a maximum period of 2 h.Muscle–ligament tissue. Before obtaining the LIVD fragments, five fragments of muscle–ligament tissue adjacent to the collected disc will be collected. The same collection and initial cooling precautions used for the disc fragments will be followed when collecting the adjacent tissue.

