### Laboratory analysis

#### Cultures

The skin swabs will be opened only in a laboratory setting. Samples will be seeded on blood agar plates (5% defibrinated sheep blood; blood agar base, 40 g/L; agar, 5 g/L) and anaerobic blood agar (5% defibrinated sheep blood; blood agar base, 40 g/L; agar, 5 g/L; hemin, 10 mL/L; menadione, 5 drops/L. After sowing in solid media, the swab will be inoculated in thioglycolate medium, where it will remain for 14 days. One of the plates will be incubated in a capnophilic atmosphere (5% to 10% CO_2_), while the other will be incubated in strict anaerobiosis (atmosphere containing 10% CO_2_,10% H_2_, and 80% N_2_) using an anaerobic chamber or Glove Box (Coy Labs^®^, USA).

The plates will be read after 24 h of incubation and, in case of growth, the colonies will be identified. In the absence of growth, they will be incubated again, and a new reading will be performed after 72 h. The thioglycolate vials containing skin swabs will be kept in a bacteriological incubator (35°C to 37°C) for 14 days. In a laboratory setting, the tubes containing disc fragments and muscle–ligament tissue will undergo vortexing (Even EVX2800-BI^®^, Brazil) for 15 s. All tubes will be kept in a bacteriological incubator (35°C to 37°C) and, after 24 h, the first subculture will be carried out using a 100 μL bacteriological loop. An aliquot of the thioglycolate will be taken and plated on blood agar and anaerobic blood agar. The first plate will be incubated in a capnophilic atmosphere and the second in strict anaerobiosis using an anaerobic chamber or Glove Box (Coy Labs^®^, USA). The plates will be read after 24 h and the colonies will be identified in case of growth. In the absence of growth, they will be incubated again, and a new reading will be performed after 72 h. The same procedure will be used for all thioglycolate vials (totaling six vials for each level approached). Thioglycolate tubes containing the clinical specimens will be kept in an oven for 14 days. Subcultures will be carried out after 72 h and always every 3 days, with the last subculture being carried out on the 14^th^ day of incubation in the same solid culture medium and atmospheres used in the first 24 h.

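### Proteomic spectra from broth cultures are searched only against *C. acnes* and human proteins, so *C. acnes* proteins may be over-called in vials with other or mixed growth

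*Protocol article*

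**What the plan says.** Under Sampling, disc tissue goes straight into culture broth: "Each fragment will be placed in a vial containing thioglycolate broth". Under Cultures, the vials are then incubated: "Thioglycolate tubes containing the clinical specimens will be kept in an oven for 14 days".

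Under Proteomics, the sample is taken from this culture: "Thioglycolate culture mediums will be centrifuged, and the sediment obtained will be washed in phosphate buffer and centrifuged again". The search space is then named: "proteins will be identified using protein banks referring to *C*. *acnes* and eukaryotes (humans"). Validation follows on the same footing: "the data will be validated using the Scaffold software version 5 for the same databases".

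Two other sections show that *C. acnes* is not the only organism expected. The primary goal in Hypotheses and objectives is to "determine the incidence of LIVD colonization by low virulent pathogens using specific sampling and culture techniques". Genotypic characterization describes two PCR phases: "The first to confirm the presence of bacteria (target and non-target").

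The proteomic result serves objective 4, a molecular profile of disc degeneration and low back pain in patients whose cultures grow *C. acnes*. The Abstract also plans multiomic analysis of both colonized and non-colonized discs.

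**The concern.** A database search can assign a spectrum only to a protein that is in the database. With two banks there are three possible results: *C. acnes*, human, or no match. If the vial also holds another bacterium, that organism's peptides have no correct candidate. Most peptides specific to it should stay unmatched, which loses identifications but does no further harm. Peptides whose sequence it shares with *C. acnes* will match well, and *C. acnes* is the only bacterium they can be credited to.

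At stake is how specific the *C. acnes* part of the molecular profile is. In a vial with mixed growth, the other organism's shared peptides add to what looks like *C. acnes* expression. In a vial that grew only another organism, *C. acnes* proteins could be listed although none are present. The Introduction gives proteomic evidence of *C. acnes* considerable weight, treating an earlier proteomic study as having ruled out contamination. The search should therefore be able to tell *C. acnes* protein from that of another bacterium.

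**Working it through.** **No plan figure to reproduce.** The Proteomics section gives no error rate, peptide threshold or number of samples. The plan's one design figure, 96 participants, follows from 1.96² × 0.5 × 0.5 / 0.10² = 96.04 (the 0.5 is assumed). It concerns the primary outcome and has no bearing here.

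**Step 1: the passages side by side.**

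| Question | What the article says | Section |
|---|---|---|
| What is analysed? | Washed sediment of the thioglycolate culture | Proteomics |
| What can be in it? | Tissue and whatever grew over 14 days | Sampling; Cultures |
| Are other bacteria expected? | Yes: low-virulence pathogens in general, and non-target bacteria | Hypotheses and objectives; Genotypic characterization |
| Is proteomics limited to pure *C. acnes* growth? | Not stated | Proteomics |
| Which bacteria are in the search bank? | *C. acnes* only | Proteomics |
| Is the bank widened at validation? | No, the same banks are used | Proteomics |

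**Step 2: what validation can do.** Validation on the same banks can remove weak or random matches. A shared peptide gives a strong match, because its sequence really is in the *C. acnes* bank. Without a rival bacterial candidate, nothing marks it as ambiguous.

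**Step 3: possible size, on assumed inputs.** Neither input below is in the documents. Let *k* be the number of identifiable peptides from the other bacterium in a vial, and *s* the share of them identical to a *C. acnes* peptide. Treating peptides as independent:

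- expected number credited to *C. acnes* = *k* × *s*
- P(at least two) = 1 − (1 − *s*)^k − *k s* (1 − *s*)^(k−1)

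| *k* | *s* | Expected *k* × *s* | P(at least two) |
|---|---|---|---|
| 200 | 0.1% | 0.2 | 0.02 |
| 200 | 1% | 2 | 0.60 |
| 200 | 5% | 10 | 0.9996 |
| 1000 | 0.1% | 1 | 0.26 |
| 1000 | 1% | 10 | 0.9995 |
| 1000 | 5% | 50 | about 1 |
| 3000 | 0.1% | 3 | 0.80 |
| 3000 | 1% | 30 | about 1 |
| 3000 | 5% | 150 | about 1 |

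These are peptides in the whole sample. Two miscredited peptides need not fall on the same protein, so the last column overstates the chance that a rule of two peptides per protein would be met. The table shows only that the answer depends on quantities the documents do not give.

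**The case against.** **Microbiology, not proteomics, decides which organism is present.** Colonization is set by culture, MALDI-TOF and 16S PCR, and objective 4 starts from patients already classified as positive for *C. acnes*. This stands, and it protects the primary outcome completely. It does not protect the content of the profile, because a culture positive for *C. acnes* can also contain another species.

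**The article does not say which vials enter proteomics.** A reader might infer that discs growing only another organism will serve as controls and show false *C. acnes* proteins there. The text does not establish this. The primary goal speaks of low-virulence pathogens in general, so such a disc might not count as non-colonized at all. The wording about discs with and without *C. acnes* is in the Metabolomics section. The comparison-group error is therefore a possibility and not a stated feature of the design.

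**Broth proteins and laboratory contaminants.** A reader might also infer that medium proteins will be taken for host response. The documents do not support this. The sediment is washed, the protein content of the broth is not given, and the wording on eukaryotes is loose enough to cover a wider bank. Contaminant lists and error thresholds are details an article commonly leaves out. None of this helps with other bacteria: neither a eukaryote bank nor a usual contaminant list would hold the bacterial species isolated.

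**A count of affected patients.** One could assume that 5% to 30% of 96 patients grow only another organism, giving 0.05 × 96 = 4.8 to 0.30 × 96 = 28.8, about 5 to 29. The percentages have no source in the documents, and the sum assumes proteomics in every patient. The result would count patients exposed, not false identifications, so it should not be cited as the size of the error.

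**The error is reversible.** The raw files can be searched again at any time. This is true and lowers the urgency, but it is also why the change costs little.

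**Conclusion.** The point holds in limited form. The article names a search space with one bacterium, repeats it at validation, and applies it to cultures in which it expects other bacteria. This is a stated rule that can give a wrong result, not a detail left to a fuller document. In vials with other or mixed growth, peptides shared with *C. acnes* can be credited to no other bacterium, so *C. acnes* proteins may be over-called in objective 4 and in the colonized versus non-colonized comparison.

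The conclusion rests on two conditions: that some vials with other or mixed growth enter proteomics, which the article neither states nor excludes, and that some of their peptides are shared with *C. acnes*. The size cannot be derived from the documents and may be anything from negligible to substantial. The primary outcome is not affected. Label: cheap improvement.

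**What to change.** Search the same raw files against one combined database that holds the human and *C. acnes* proteins and every other bacterial species the study identifies by MALDI-TOF. Add medium proteins and common contaminants if they are not already included. Run the validation step on that combined database. Count a *C. acnes* protein only when it is supported by peptides unique to *C. acnes* within it.

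This needs a change of database and one reporting rule, with no new samples or instrument time. The drawback is somewhat fewer identifications, because the search space is larger and shared peptides no longer count as evidence for *C. acnes*.

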#### Metabolomics

The metabolomic analysis in this study will use intervertebral disc fragments with and without isolated *C*. *acnes*. The tubes containing the disc fragments in thioglycolate liquid culture medium will be centrifuged and the sediment will be transferred to 2 mL flat-bottom polypropylene tubes containing a titanium bead (one per tube). The liquid content of these tubes will be evaporated by centrifugation with the CentriVap SpeedVac apparatus (Labconco Corporation^®^, USA) and then weighed to determine the dry weight. The tubes will then have 500 μL of MS Grade (Fluka) acetonitrile added followed by Bead Beater agitation (Biospec Product^®^, USA) (4 x 30 s). When all the material has been dissolved, the tubes will be centrifuged, and the supernatant will be stored at −80°C in new sterile tubes. To identify the metabolites, the material will be injected into a high-resolution mass spectrometer (UHPLC Q-TOF MS/MS). The data obtained will be analyzed in the Metaboanalyst 5.0 database [https://www.metaboanalyst.ca/] and its functions and interactions in the STRING software version 11 [57].

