## Abstract

Lumbar disc degeneration (LDD) and low back pain (LBP) are two conditions that are closely related. Several studies have shown *Cutibacterium acnes* colonization of degenerated discs, but whether and how these finding correlates with LBP is unknown. A prospective study was planned to identify molecules present in lumbar intervertebral discs (LLIVD) colonized by *C*. *acnes* in patients with LDD and LBP and correlate them with their clinical, radiological, and demographic profiles. The clinical manifestations, risk factors, and demographic characteristics of participants undergoing surgical microdiscectomy will be tracked. Samples will be isolated and pathogens found in LLIVD will be characterized phenotypically and genotypically. Whole genome sequencing (WGS) of isolated species will be used to phylotype and detect genes associated with virulence, resistance, and oxidative stress. Multiomic analyses of LLIVD colonized and non-colonized will be carried out to explain not only the pathogen’s role in LDD, but also its involvement in the pathophysiology of LBP. This study was approved by the Institutional Review Board (CAAE 50077521.0.0000.5258). All patients who agree to participate in the study will sign an informed consent form. Regardless of the study’s findings, the results will be published in a peer-reviewed medical journal. Trials registration number NCT05090553; pre-results.

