### Selection of outcomes

#### Primary outcome

The main objective of this study will be to determine the incidence of intervertebral disc colonization by *C*. *acnes* in patients with LBP and LDD. Positive cultures will be used to confirm colonization, followed by phenotypic and genotypic confirmation of the isolated pathogen by mass spectrometry (Biotyper) and rDNA-16s PCR analysis, respectively.

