### Modic changes

The presence of Modic type 1 changes will be considered in the evaluation of magnetic resonance images. This change is characterized by the presence of a high signal on T2-weighted sequences, with reduced signal on T1-weighted sequences [1, 2]. The frequency of Modic type 1 changes in the participants will be calculated for each of the research groups (presence or absence of colonization) and for the total number of discs analyzed in the laboratory.

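### The metabolomic comparison is stated by disc in one place and by fragment in another, so culture-negative fragments of a colonized disc can fall into the comparison group

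*Protocol article*

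**What the plan says.** The protocol article describes the units as follows.

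- **Abstract: the disc.** "Multiomic analyses of LLIVD colonized and non-colonized will be carried out".
- **Modic changes: colonization status.** The research groups are defined by whether colonization is present or absent.
- **Hypotheses and objectives, fourth further objective: the patient.** The aim is to "identify a molecular profile for LDD and LBP in patients with positive cultures for" *C. acnes*. No comparator is named.
- **Metabolomics: the fragment.** "The metabolomic analysis in this study will use intervertebral disc fragments with and without isolated" *C. acnes*.
- **Proteomics: no grouping unit.** "Thioglycolate culture mediums will be centrifuged, and the sediment obtained will be washed in phosphate buffer and centrifuged again". The section does not say whether the material is grouped by fragment, disc or patient.

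Two further statements matter. In Sampling, "Five fragments will be collected at each level approached during surgery", and "Each fragment will be placed in a vial containing thioglycolate broth". Under Cultures the vials are subcultured individually, so each fragment has its own result. Under Primary outcome, "Positive cultures will be used to confirm colonization", but no number of positive vials is set.

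**The concern.** The label of one and the same sample depends on which section is followed. Take a disc with two positive and three negative vials, and suppose two positive vials suffice to call it colonized. Under the Abstract all five fragments belong to the colonized group. Under a literal reading of Metabolomics the three negative fragments belong to the group without an isolate.

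Two things are at stake.

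1. **Dilution.** The study seeks a molecular signature linked to the presence of the pathogen in the disc. If the host reacts across the whole disc, negative fragments of a colonized disc carry that reaction, and using them as comparators pulls the two groups together.
2. **Dependence.** The same patient can then supply samples to both groups. The Statistical analysis methodology section compares two groups with tests for independent samples. Its paired tests are described for measurements at different assessments, not for fragments of one disc.

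The section on host multiomic characteristics also plans to relate disc molecules to blood molecules. Blood is a patient-level sample and cannot carry a fragment label.

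**Working it through.** The plan gives no figure for this comparison. Its sample size of 96 concerns the precision of the colonization incidence and does not enter here. The question is what share of the fragments without an isolate would come from colonized discs under the fragment reading.

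**Inputs**
- Fragments per level: 5 (Sampling). One level per patient is assumed.
- *c*, the proportion of discs colonized: not given. Range used: 46% (cited in the Introduction for anaerobes, not for *C. acnes* alone), 20% (assumed) and 3.4% (cited in the Introduction for *C. acnes*).
- *q*, the fraction of a colonized disc's five fragments that are positive: not given. Range used: 1/5 to 5/5.
- All negative fragments are taken to be assayed.

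**Formula**

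Share *f* = 5c(1 − q) / [5c(1 − q) + 5(1 − c)]. The fives cancel, so only the fraction positive matters.

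Example with c = 0.46 and q = 0.2: 0.46 × 0.8 / (0.46 × 0.8 + 0.54) = 0.368 / 0.908 = 0.405.

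| Positive of 5 | c = 46% | c = 20% | c = 3.4% |
|---|---|---|---|
| 1 | 41% | 17% | 2.7% |
| 2 | 34% | 13% | 2.1% |
| 3 | 25% | 9% | 1.4% |
| 4 | 15% | 5% | 0.7% |
| 5 | 0% | 0% | 0% |

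**Second model as a check.** Let each fragment of a colonized disc be positive independently with probability *s*, and call a disc colonized if at least one of five is positive. The expected number of negative fragments per colonized disc is [5(1 − s) − 5(1 − s)^5] / [1 − (1 − s)^5]. This gives 3.51 at s = 0.2, 2.83 at 0.4, 1.97 at 0.6 and 1.00 at 0.8. From s = 0.2 to s = 0.8 the share runs from 37% to 15% at c = 46%, from 15% to 5% at c = 20%, and from 2.4% to 0.7% at c = 3.4%. At s = 1 it is zero. The two models agree closely.

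**Effect on the contrast.** Suppose colonization shifts a metabolite by Δ in every fragment of a colonized disc. The positive group then has mean shift Δ and the group without an isolate has mean shift fΔ. The observed contrast is Δ(1 − f), so it shrinks by the share in the table. If the response is confined to the positive fragment, there is no such dilution.

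**The case against.** The strongest reply is that the Metabolomics sentence names the material and does not allocate it. It can mean fragments from culture-positive and culture-negative discs, which fits the Abstract and the grouping under Modic changes. No section uses the term control group for this comparison. That stands: a reader might infer that negative fragments of colonized discs will be used as controls, but the article does not say so. What remains is that the sentence attaches the isolate to the fragment, each fragment has its own culture result, and nothing keeps such fragments out.

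Several limits on scope also stand.

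- Only Metabolomics uses the fragment as unit, so the point does not extend to the whole multiomic programme.
- The objective on the molecular profile names no comparator and is not a rival definition of the groups.
- No section reports how often a colonized disc has mixed vials, so mixed discs cannot be called common.
- A single positive vial of five may itself be contamination, which the study sets out to assess. If so, the other four fragments dilute nothing.
- The list of tests is generic and does not assign an independent-groups test to metabolomic data, which go to Metaboanalyst. The dependence problem is therefore conditional as well.

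Finally, the choice of fragments for assay may be detailed in a fuller document. That would answer an omission, but the printed sections name different units, and any fuller document would have to settle which one governs.

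**Conclusion.** The unit of the metabolomic comparison is inconsistent: colonized against non-colonized discs in the Abstract, fragments with and without an isolate in Metabolomics. Followed literally, the second allows negative fragments of a colonized disc into the comparison group.

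The size is unknown because it turns on within-disc concordance. It could be material if colonization is frequent and discs are mixed, is negligible at 3.4% colonization, and is nil if all five fragments of a colonized disc are positive. A reader might take 41% as the expected contamination of the comparison group. The documents do not support that. It needs 46% colonization (a rate for anaerobes), one positive fragment in five and every negative fragment assayed; an equal loss of contrast also needs a disc-wide response.

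**What to change.** 1. Under Primary outcome, state how many positive vials make a disc colonized. This needs a decision, since no threshold is printed now.
2. Under Metabolomics, take comparison fragments only from discs in which all five disc vials are *C. acnes*-negative. A disc with some positive vials but fewer than the threshold would also stay out of that group.
3. Use negative fragments of culture-positive discs only in a separate, paired within-disc comparison.
4. Where levels of one patient differ in status, account for patient in the analysis. Grouping by disc alone does not remove that dependence.
5. Under Proteomics, state the same grouping.

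Apart from the threshold decision the change is one of wording, and it needs no new samples. The cost is fewer comparison fragments: relative to the literal fragment reading, the loss is the share in the table, and it is largest when colonization is common and discs are mixed.
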